## Abstract

**Background**: Management of patients with radioiodine (RAI)-refractory differentiated thyroid cancer (DTC) is a challenge as I-131 therapy is deemed ineffective while standard-of-care systemic therapy with tyrosine kinase inhibitor (TKI) lenvatinib is associated with frequent toxicities leading to dose reductions and withdrawal. A potential new treatment approach is to use TKIs as redifferentiation agent to restore RAI uptake to an extent that I-131 therapy is warranted. Prior studies show that short-term treatment with other TKIs restores RAI uptake in 50–60% of radioiodine-refractory DTC patients, but this concept has not been investigated for lenvatinib. Furthermore, the optimal duration of treatment with TKIs for maximal redifferentiation has not been explored. **Methods and Design**: A total of 12 patients with RAI-refractory DTC with an indication for lenvatinib will undergo I-124 PET/CT to quantify RAI uptake. This process is repeated after 6 and 12 weeks post-initiating lenvatinib after which the prospective dose estimate to target lesions and organs at risk will be determined. Patients will subsequently stop lenvatinib and undergo I-131 treatment if it is deemed effective and safe by predefined norms. The I-124 PET/CT measurements after 6 and 12 weeks of the first six patients are compared and the optimal timepoint will be determined for the remaining patients. In all I-131 treated patients post-therapy SPECT/CT dosimetry verification will be performed. During follow-up, clinical response will be evaluated using serum thyroglobulin levels and F-18 FDG PET/CT imaging for 6 months. It is hypothesized that at least 40% of patients will show meaningful renewed RAI uptake after short-term lenvatinib treatment. **Discussion**: Shorter treatment duration of lenvatinib treatment is preferred because of frequent toxicity-related dose reductions and drug withdrawals in long-term lenvatinib treatment. Short-term treatment with lenvatinib with subsequent I-131 therapy poses a potential new management approach for these patients. Since treatment duration is reduced and I-131 therapy is more tolerable for most patients, this potentially leads to less toxicity and higher quality of life. Identifying RAI-refractory DTC patients who redifferentiate after lenvatinib therapy is therefore crucial. **Trial Registration**: ClinicalTrials.gov, NTC04858867.

## 1. Background

Thyroid cancer is the most common endocrine malignancy, accounting for approximately 3.1% of all cancer diagnoses worldwide and an estimated 41,000 deaths in 2018 [1]. The majority of cases are suffering from differentiated thyroid cancer (DTC), which is commonly managed by total thyroidectomy and subsequent radioiodine-131 (I-131) therapy and is associated with excellent long-term survival [2,3]. The effectiveness of I-131 therapy is dependent on the ability of cancer tissue to take up and retain radioiodine (RAI) after which the tissue structure is damaged by radiation. The sodium iodide symporter (NIS) plays a pivotal role in the uptake and retention of iodine in thyrocytes and thyroid cancer cells [4,5,6,7].

The function to take up and retain iodine is initially or gradually lost in 5–15% of all DTC cases and up to 50% of cases with metastases [6,8], indicating a state of dedifferentiation that is known as RAI-refractory disease [7]. To prevent futile repeated I-131 therapy and consider more effective treatments, it is crucial to identify RAI-refractory DTC early. Currently, diagnosis is merely based on imaging and response to I-131 therapy [9]. While criteria have been developed over time, the definition of RAI-refractory DTC is still controversial. The disease can be diagnosed when a patient complies to at least one of the following criteria: no RAI uptake present on diagnostic or therapeutic RAI scintigraphy (in some or all known lesions), progression of metastases despite RAI uptake or patients reaching a cumulative prescribed I-131 activity of >22.2 GBq [9,10]. In all RAI-refractory DTC patients, I-131 therapy is no longer deemed effective. One major pitfall in the current definition is the lack of assessment of the extent of RAI uptake by the lesions. This would require a dosimetry approach but is not yet embedded in routine clinical practice.

Management of RAI-refractory DTC patients is a considerable challenge in clinical practice. Therefore, the disease is associated with a poor overall prognosis: the 10-year survival rate is less than 10% and the mean life expectancy only 3–5 years [11]. Systemic therapy with the oral multi-receptor tyrosine kinase inhibitor (TKI) lenvatinib is approved for progressive RAI-refractory DTC and currently standard practice. Further systemic treatment options are limited. Though a response rate of 65% and improved median progression-free survival in comparison to placebo (18 months versus 3.6 months) is observed [12], the toxicity burden associated with lenvatinib should be taken into consideration, as this may significantly compromise the patients’ quality of life [4,13]. Treatment should, therefore, continue as long as clinical benefit is observed or until unacceptable toxicity occurs [10]. According to real-life data, toxicity is frequently observed leading to dose reductions in 56% of patients and toxicity-related drug withdrawal in 44% of patients [14].

A potential alternative way to achieve disease control in RAI-refractory thyroid cancer is to restore RAI uptake using TKIs as redifferentiation agents [15]. The re-induced RAI uptake enables the possibility to subsequently treat patients with I-131, thereby reducing the administration duration of TKIs and subsequent adverse events. Several clinical studies have already shown the ability of TKIs, including selumetinib, trametinib, vemurafenib, dabrafenib and larotrectinib to re-induce RAI uptake in RAI-refractory thyroid cancer patients [16,17,18,19,20]. These studies showed that after short-term therapy of approximately 4 weeks with these TKIs, renewed or enhanced RAI uptake was observed in 35–67% of RAI-refractory patients. Subsequently, I-131 therapy was initiated in 35–71% of all patients [16,17,18,19,20,21,22,23].

The TKIs for which this redifferentiation effect is observed are all selectively targeting either mitogen-activated protein kinase kinase (MEK), B-type rapidly accelerated fibrosarcoma kinase (BRAF) mutations or neurotrophic tyrosine receptor kinase rearrangements, thereby downstream inhibiting the mitogen-activated protein kinase (MAPK) pathway. In contrast, lenvatinib inhibits multiple receptor tyrosine kinases including vascular endothelial growth factor receptor (VEGFR1-3), fibroblast growth factor receptor (FGFR1-4), platelet-derived growth factor receptor α (PDGFRα) and rearranged during transfection (RET), further inhibiting induced signaling through the MAPK and PI3K/Akt pathways [24]. As aberrant activation of MAPK and phosphatidylinositol-3-kinase (PI3K)/protein kinase B (Akt) pathways inhibits NIS transcription and is associated with decreased NIS messenger ribonucleic acid (mRNA) expression [4], lenvatinib is hypothesized to restore functional NIS expression and thereby enhance iodine accumulation. An in vitro study by Anschlag et al. showed that technetium-99 m uptake (as a surrogate for NIS expression) was increased with a maximum of 326% in a well-differentiated human papillary thyroid carcinoma cell line after exposure to lenvatinib, but smaller effects were observed in poorly differentiated thyroid carcinoma cell lines [25]. They state that ‘the final proof for a redifferentiating potential of lenvatinib is incomplete’ based on their studies [25]. As experimental TKIs are currently not available to all patients, in contrast to the approved lenvatinib that is already part of standard clinical care and embedded in current guidelines [10], we believe evaluating its redifferentiation effect is very useful as it could prove to be a game-changer in the management of RAI-refractory DTC. Little is known about how long this redifferentiation effect lasts and whether it increases or decreases with increasing treatment duration. It is therefore of interest to investigate whether duration of treatment is of influence in the extent of renewed or increased RAI uptake after lenvatinib treatment in this trial.

The focus in this trial will be to evaluate the ability of lenvatinib to redifferentiating RAI-refractory DTC to an extent that functional RAI uptake is restored and I-131 therapy is justified. We will objectify this by quantitative molecular imaging and will predict efficacy and toxicity of radioiodine-131 based on dosimetry. We hypothesize that at least 40% of the patients will show sufficient redifferentiation for subsequent meaningful I-131 therapy. Since this would imply reduced lenvatinib treatment duration and since I-131 therapy is generally better tolerated by patients, this potentially leads to a new, less toxic treatment approach with higher quality-of-life.

## 2. Methods and Design

### 2.1. Study Design

This is a single-center open label phase II study evaluating the effect of short-term lenvatinib treatment for restoring RAI uptake and retention in RAI-refractory thyroid cancer to warrant I-131 therapy.

### 2.2. Trial Organization and Coordination

The RESET trial has been designed by the study initiators at the Department of Medical Oncology and the Department of Radiology, section Nuclear Medicine, at the Leiden University Medical Center (LUMC). Both departments are responsible for the overall trial management, database management and quality assurance including monitoring and reporting. The Department of Clinical Pharmacy and Toxicology is responsible for dispensing and quality assurance regarding the use of I-124.

### 2.3. Ethics, Informed Consent and Monitoring

This study has been approved by the Medical Ethics Committee Leiden-Den Haag-Delft (P20.096) and is registered on ClinicalTrials.gov (NTC04858867). This study complies with the Helsinki Declaration, the Medical Association code of conduct, the principles of Good Clinical Practice (GCP) and the General Data Protection Regulation. This trial will be carried out following local legal and regulatory requirements. All patients must declare their informed consent to participate in the trial in written form before enrollment. An independent monitoring committee appointed by the LUMC will perform on-site monitoring of recruited patients according to the International Conference on Harmonization (ICH) Harmonized Tripartite Guideline for GCP.

### 2.4. Sample Size Calculation

The study requires 12 patients of which 5 (42%) are expected to show meaningful renewed uptake of radioiodine to confirm that the real fraction is at least 15% (binomial distribution 95%-confidence interval: 15.2–72.3%).

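### Section 2.4 treats the expected 5 of 12 as if it will be observed, but 5 is also the minimum that excludes 15%, so the chance of doing so is only 56–61% at the planning rates

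*Protocol article*

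**What the plan says.** The sample-size argument in Section 2.4 is one sentence. It asks for 12 patients, of whom "5 (42%) are expected to show meaningful renewed uptake of radioiodine to confirm that the real fraction is at least 15" per cent, and supports this with "binomial distribution 95%-confidence interval: 15.2–72.3" per cent. It gives no probability of obtaining 5 or more.

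The expected rate agrees with the hypothesis stated elsewhere. Section 1 says "We hypothesize that at least 40% of the patients will show sufficient redifferentiation for subsequent meaningful I-131 therapy", and the Abstract says "It is hypothesized that at least 40% of patients will show meaningful renewed RAI uptake after short-term lenvatinib treatment". As a reference range from other kinase inhibitors, Section 1 reports that "renewed or enhanced RAI uptake was observed in 35–67% of RAI-refractory patients".

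**The concern.** An expected count is the centre of a distribution. If about 5 of 12 are expected, then 4, 3 or fewer are ordinary results. A size argument that computes the interval at the expected count alone works only if smaller counts would serve the purpose too, or if their probability is stated. Here they would not serve it if 5 is the lowest count that excludes 15%, and their probability is not stated.

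At stake is what the reader believes the trial can deliver on its primary endpoint. The sentence presents 12 patients as the number required to confirm a fraction of at least 15%. If the chance of doing so is not far above one half at the protocol's own planning rates, the reader should be told that before results exist.

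**Working it through.** **Inputs.** n = 12, expected count 5, rate to be excluded 15%, and a two-sided 95% interval (0.025 in the lower tail), all from Section 2.4. The hypothesised rate of at least 40% is in the Abstract and Section 1. The range 35–67% with other agents is in Section 1.

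**Step 1: reproduce the printed interval.** The Clopper-Pearson lower limit for x of n is the value p at which P(X ≥ x | n, p) = 0.025. The upper limit is the value at which P(X ≤ x | n, p) = 0.025. For 5 of 12 this gives 15.17% and 72.33%, matching the document. Wilson (19.3–68.1%) and Wald (13.8–69.6%) do not match, so the exact interval was used.

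**Step 2: find the smallest count that excludes 15%.** The exact lower limit exceeds 15% only when P(X ≥ x | 12, 0.15) is below 0.025.

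| Responders of 12 | P(X ≥ x) at a true 15% | Exact 95% lower limit |
|---|---|---|
| 4 | 0.0922 | 9.9% |
| 5 | 0.0239 | 15.2% |

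So 5 is the minimum, and the one-sided type I error of that criterion at 15% is 2.4%. The threshold does not depend on the choice of interval: 4 of 12 also falls short with a one-sided 95% exact bound (12.3%) and with Wilson (13.8%).

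**Step 3: probability of reaching the minimum.** P(X ≥ 5) = 1 − Σ C(12, k) p^k (1 − p)^(12−k), summed over k = 0 to 4. At p = 0.40 the terms are:

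- k = 0: 0.6^12 = 0.0022
- k = 1: 12 × 0.4 × 0.6^11 = 0.0174
- k = 2: 66 × 0.4^2 × 0.6^10 = 0.0639
- k = 3: 220 × 0.4^3 × 0.6^9 = 0.1419
- k = 4: 495 × 0.4^4 × 0.6^8 = 0.2128

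The sum is 0.4382, so P(X ≥ 5) = 0.5618. The same formula at other rates gives:

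| True fraction | P(at least 5 of 12) | P(4 or fewer) |
|---|---|---|
| 35% | 0.417 | 0.583 |
| 40% | 0.562 | 0.438 |
| 5/12 (41.7%) | 0.608 | 0.392 |
| 50% | 0.806 | 0.194 |
| 60% | 0.943 | 0.057 |
| 67% | 0.982 | 0.018 |

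At the planned 5/12 the trial would fail to exclude 15% about 39% of the time. At a true 40% it would fail about 44% of the time.

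**The case against.** The strongest reply is that nothing printed is wrong. The interval is exact, and Section 2.4 claims no power. This is a small proof-of-concept study, the article condenses a longer protocol, and operating characteristics may be given there. All of that stands as a defence of the interval and against any charge of omission. It does not rescue the claim that is stated here, namely that 12 patients are what is required to confirm at least 15%.

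A second reply is that the hypothesis is at least 40%, so 56% is its floor, and at 50% or 60% the chances are good (81% and 94%). This also stands, and it is why the figure should be given across a range. However, Section 2.4 itself plans on 5/12, where the probability is 61%, and the cited range for other agents reaches down to 35%, where it is 42%.

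A reader might go further and infer that the 40% hypothesis contradicts the 15% criterion, because a lower limit above 40% would need 9 of 12 (42.8%). The document does not support that. Expecting about 40% while excluding 15% is an ordinary pairing of alternative and null rates, and no section says that 40% will be tested. A reader might also infer that 5 of 12 would be presented as proof of 40%, or 4 of 12 as failure. Section 2.4 ties 5 of 12 only to 15% and prints the wide interval beside it, and neither Section 2.4 nor Section 2.9 sets a pass/fail rule.

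**Conclusion.** The point holds as a moderate misstatement of what the sample size delivers. The expected count and the minimum count needed are the same number, so the stated purpose is met with probability 56% at a true 40% and 61% at the planning rate. It is neither an error in the interval nor a contradiction between 40% and 15%.

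This rests on four assumptions: the fraction in Section 2.4 is the primary endpoint of Section 2.6; all 12 patients are evaluable; outcomes are independent with one common probability across both cohorts; and confirming at least 15% means that the lower limit of the printed type of interval exceeds 15%. Losing a patient would make matters worse: with 11 evaluable, 5 responders are still needed (lower limit 16.7%).

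**What to change.** Keep n = 12 and the interval. Restate Section 2.4 along these lines:

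> With 12 patients, at least 5 eligible patients are needed for the exact 95% lower limit to exceed 15% (5/12: 15.2–72.3%; one-sided type I error 2.4% at a true 15%). The probability of this is 56% if the true fraction is 40%, 61% if it is 5/12 and 81% if it is 50%.

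In the same place, describe 40% as the expected rate and 15% as the rate the trial is designed to exclude. Use the same labels where the Abstract and Section 1 state the hypothesis.

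This adds no patients and changes neither conduct nor analysis. It sets out what the interval argument already implies and does not create a new pass/fail rule. The cost is that the justification looks less favourable. For scale only, with the same exact criterion an 80% chance at a true 40% is first reached at 24 patients (at least 8 responders, 0.808). That increase is not requested here.

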### 2.5. Study Overview

Patients with RAI-refractory (determined by the multidisciplinary tumor board) DTC with the intention of starting standard-of-care lenvatinib treatment will be included in this study. Prior to lenvatinib treatment, patients will undergo recombinant human thyroid-stimulating hormone TSH (rhTSH)-stimulated I-124 dosimetry to quantify RAI uptake and retention at baseline. Besides that, patients undergo F-18 fluorodeoxyglucose (FDG) positron emission tomography (PET)/computed tomography (CT) and a biopsy is performed. An additional biopsy is performed after 6 weeks of lenvatinib treatment. The first half of the intended sample size (cohort 1, N = 6) will be treated with lenvatinib for a total of 12 weeks (Figure 1). After 6- and 12-week treatment, patients will undergo rhTSH-stimulated I-124 dosimetry to evaluate the redifferentiation effect and to assess expected absorbed lesion doses and the maximum tolerable activity (MTA). Patients will undergo subsequent rhTSH-stimulated I-131 therapy with the MTA (or a maximum of 7.4 GBq) if a clinically meaningful lesion dose (≥20 Gy) is expected. For all patients eligible for I-131 therapy, lenvatinib is discontinued prior to administration of I-131 and post-therapeutic I-131 dosimetry will be performed for dose verification. Results between 6- and 12-week lenvatinib treatment will be compared to select the lenvatinib treatment duration that leads to highest extent of redifferentiation. The next 6 patients (cohort 2) will then receive lenvatinib for either 6 or 12 weeks. Patients who are not eligible for I-131 therapy, will continue lenvatinib treatment at the discretion of the treating physician, effectively undergoing standard-of-care treatment. Patients will be followed up according to current guidelines for a total of 9 months after start of lenvatinib treatment. In case of progression after RAI, lenvatinib treatment will be restarted as standard of care. Metabolic and biochemical response will be assessed using F-18 FDG PET/CT and thyroglobulin (Tg) levels, respectively. An overview of all study procedures is given in Table 1.

### 2.6. Study Endpoints

The primary endpoint of the study is the fraction of RAI-refractory thyroid cancer patients that is eligible for I-131 therapy after 6- or 12-week lenvatinib treatment to an extent that clinically meaningful tumor radiation doses can be safely delivered with acceptable I-131 doses as determined by I-124 dosimetry of both lesions and healthy organs at risk.

Secondary endpoints include:Extent of RAI uptake at baseline and after 6- or 12-week lenvatinib;Optimal duration of lenvatinib treatment (6 weeks or 12 weeks) for maximum redifferentiation;Agreement between expected absorbed dose per lesion predicted by I-124 PET/CT dosimetry and actual absorbed dose per lesion determined by intra-therapeutic I-131 single photon emission computed tomography (SPECT)/CT dosimetry in patients in which I-131 therapy is warranted;Metabolic and biochemical treatment response using F-18 FDG PET and unstimulated (thyroid-stimulating hormone (TSH)-suppressed) Tg levels, respectively;Progression free survival, best objective response and overall survival;Incidence and severity of toxicities according to the Common Terminology Criteria for Adverse Events (CTCAE) 5.0;Quality of life (QoL).

An explorative endpoint of this study is to evaluate alterations at the transcriptional and translational level in biopsied tumor lesions before and after 6-week lenvatinib treatment and to determine whether treatment response is related to genetical profiles.

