#### 2.8.4. I-131 Therapy

The redifferentiation effect will be evaluated by quantification of RAI uptake and assessment of corresponding expected dose to lesion and organs at risk per administered GBq I-131 [Gy/GBq]. Patients are eligible for I-131 therapy with MTA (maximized at 7.4 GBq) if:A clinically meaningful lesion dose is expected: ≥20 Gy in at least one lesion;Acceptable toxicity is expected: blood dose ≤2 Gy and 48 h post-administration body retention ≤3.0 GBq–4.4 GBq (with and without lung metastases).

If considered effective and safe, lenvatinib will be discontinued and standard-of-care I-131 therapy will be given after rhTSH stimulation. Patient preparations are identical to the preparations performed prior to the I-124 dosimetry procedures, including rhTSH administration and dietary restrictions. After ingestion of I-131, patients stay within the hospital considering radiation protection measures and are monitored during their stay until dose-rates are below the local limit for discharge. 

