^i^: standard procedures, ^ii^: only provided to patients eligible for I-131 therapy; ^iii^: only provided to patients in cohort 1.^a^: Hematology: Hb, platelet count, absolute neutrophil count (ANC), white blood cell diff, hematocrit, PT/INR, APTT. Chemistry: LDH, phosphorus, sodium, potassium, magnesium, chloride, calcium, creatinine, albumin, total protein, SGOT (AST), SGPT (ALT), bilirubin (indirect + direct), GGT, alkaline phosphatase, glucose, amylase, lipase, TSH, fT4, thyroglobulin. ^b^: prior to I-124 administration of 37 (±10%) MBq, 0.9 mg Thyrotropin alfa injections are given on 2 consecutive days. At 24 ± 6 and 96–120 h post-administration of I-124, PET/CT imaging is performed. Blood draws and whole body counting are performed at 2–4, 24 ± 6 and 96–120 h post-administration. ^c^: prior to I-131 administration, 0.9 mg Thyrotropin alfa injections are given on 2 consecutive days. The MTA (≤7.4 GBq) I-131 is administered to the patient after which a stay in the hospital is required for an expected 4–5 days. ^d^: SPECT/CT imaging is performed at 24 ± 6, 48 ± 6, 72 ± 6 and 144 ± 24 h post-administration. Blood draws and whole-body counting will be performed at 2–4, 6 ± 1, 24 ± 6, 96 ± 12 and 144 ± 24 h post-administration. ^e^: At 12, 24 and 36 weeks after initiation of lenvatinib, F-18 FDG PET/CT will be performed. In all patients treated with I-131, an evaluation will also be performed 6 months after I-131 therapy.

**Table 2 diagnostics-12-03154-t002:** Inclusion- and exclusion criteria of the RESET trial.

Inclusion Criteria	
General	Age ≥18 years ECOG performance status ≤2 Life expectancy ≥3 months Agreement to use a highly effective method of contraception during the study
Tumor characteristics	Histologically or cytologically confirmed DTC Progressive (biochemical or anatomic) disease for which lenvatinib is indicated RAI-refractory disease on structural imaging, defined as: - Metastatic lesions that are not RAI-avid on a diagnostic or intra-therapeutic RAI scan performed prior to enrolment in the current study - RAI-avid metastatic lesions which remained stable in size or progressed according to RECIST 1.1 criteria despite RAI treatment. Absence of response is observed during 6–9 months after high dose I-131 therapy. Measurable disease on ceCT prior to inclusion according to RECIST 1.1: - ≥1.0 cm in the longest diameter for a non-lymph node - ≥1.5 cm in the short axis for a lymph node

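### The primary endpoint (2.6) counts I-131 eligibility after lenvatinib whatever the baseline status, so it is not the renewed uptake to which the 5-of-12 against 15% criterion (2.4) refers

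*Protocol article*

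**What the plan says.** All references are to the protocol article.

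- **Aim (2.1):** the trial is "evaluating the effect of short-term lenvatinib treatment for restoring RAI uptake and retention in RAI-refractory thyroid cancer". The Background puts the hypothesis in the same terms: "We hypothesize that at least 40% of the patients will show sufficient redifferentiation for subsequent meaningful I-131 therapy".
- **Sample size (2.4):** "The study requires 12 patients of which 5 (42%) are expected to show meaningful renewed uptake of radioiodine", in order "to confirm that the real fraction is at least 15% (binomial distribution 95%-confidence interval: 15.2–72.3"%).
- **Primary endpoint (2.6):** "the fraction of RAI-refractory thyroid cancer patients that is eligible for I-131 therapy after 6- or 12-week lenvatinib treatment".
- **Eligibility rule (2.8.4):** "A clinically meaningful lesion dose is expected: ≥20 Gy in at least one lesion", together with limits on blood dose and whole-body retention, at an activity capped at 7.4 GBq. It is an absolute rule and requires no change from baseline.
- **Entry (Table 2 and 2.7):** one route to the refractory label is "RAI-avid metastatic lesions which remained stable in size or progressed according to RECIST 1.1 criteria despite RAI treatment". The first 12 consenting patients who meet Table 2 are enrolled. Table 2 has no criterion based on I-124 dosimetry.
- **Baseline measurement (2.5, 2.8.3):** every patient has I-124 dosimetry before lenvatinib, covering lesions, blood and whole body.
- **Analysis (2.9):** values before lenvatinib are compared with those during or after it by paired tests, with McNemar's test for the eligible fraction and the Wilcoxon signed-rank test for numeric dosimetry.

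**The concern.** Sections 2.4 and 2.6 name different quantities. The first counts patients who "are expected to show meaningful renewed uptake of radioiodine", which implies a change. The second counts a state after treatment. They coincide only if no enrolled patient meets the eligibility rule before lenvatinib, and the entry criteria do not ensure that. A patient admitted through the RAI-avid route needs just one lesion at 20 Gy or more to satisfy the dose part of the rule, and could do so at baseline.

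Followed literally, 2.6 scores that patient as a success, and the fraction is then read as evidence of redifferentiation. With 12 patients and a criterion met by the narrowest margin, a single misattributed success can decide the primary conclusion.

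**Working it through.** **1. The plan's own figure.** Inputs: x = 5, n = 12 (2.4). The exact (Clopper-Pearson) 95% interval is

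- lower limit = 2.5% quantile of Beta(x, n − x + 1) = Beta(5, 8): 15.17%
- upper limit = 97.5% quantile of Beta(x + 1, n − x) = Beta(6, 7): 72.33%

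This reproduces 15.2–72.3%. Five is the smallest count that works, since 4/12 has a lower limit of 9.9%. If the true rate is 15%, P(X ≥ 5 | n = 12) = 2.4%.

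**2. One or two baseline-eligible patients among five successes.**

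| Already eligible at baseline | New conversions, of all 12 (95% CI) | New conversions, of those at risk (95% CI) |
|---|---|---|
| 0 | 5/12 (15.2–72.3%) | 5/12 (15.2–72.3%) |
| 1 | 4/12 (9.9–65.1%) | 4/11 (10.9–69.2%) |
| 2 | 3/12 (5.5–57.2%) | 3/10 (6.7–65.3%) |

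With one such patient, the lower limit for renewed uptake is already below 15% on either denominator.

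**3. Chance of reaching 5 of 12 as the endpoint is written.** Let q be the share eligible at baseline and c the conversion rate among the rest. Baseline-eligible patients are assumed to stay eligible. The post-treatment rate is p = q + (1 − q)c, and the chance is P(X ≥ 5 | 12, p). The documents do not give q, so the range is an assumption.

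| q | c = 0 (no conversions) | c = 15% |
|---|---|---|
| 0% | 0% | 2.4% |
| 10% | 0.4% | 12.8% |
| 15% | 2.4% | 21.9% |
| 20% | 7.3% | 33.1% |
| 30% | 27.6% | 57.6% |

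Example: q = 20% and c = 15% give p = 0.20 + 0.80 × 0.15 = 0.32, hence 33.1%. Counting only new conversions among all 12, the rate is 0.80 × 0.15 = 0.12 and the chance is 0.95%. With no conversions at all, the chance exceeds the design's 2.4% only when q is above 15%.

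**4. What the McNemar test adds.** With k conversions and no losses, the exact two-sided p-value is 2 × 0.5^k.

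- k = 5: p = 0.0625
- k = 6: p = 0.031

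Six conversions are therefore needed. At a 40% conversion rate, with all 12 ineligible at baseline, P(X ≥ 6 | 12) = 33.5%, against P(X ≥ 5 | 12) = 56.2% for the criterion in 2.4.

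The article does not say which form of the test is meant. The continuity-corrected statistic, (5 − 1)²/5 = 3.2, is below 3.84; the uncorrected one, 5²/5 = 5, is above it. With five discordant pairs the exact form is the safer basis.

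**The case against.** **The planned analysis already uses baseline.** This is the strongest objection, and much of it stands. Section 2.9 calls the eligible fraction the primary endpoint and compares it before and after lenvatinib by McNemar's test. A patient eligible on both occasions adds nothing to that test. The Wilcoxon comparison and the secondary endpoint on extent of uptake also bear on restoration. A reader might infer that the trial cannot show restored uptake; the documents do not support that. What remains is that 2.9 leaves the fraction in 2.6 and the criterion in 2.4 as they are. McNemar's null hypothesis is also no net change, not a rate of 15%.

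**Section 2.4 already speaks of renewed uptake.** This shows what was intended. It does not put the condition into 2.6, and the article does not say which count is set against 15%.

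**The baseline-eligible share may be negligible.** This stands. Patients have progressive disease judged refractory by the tumour board, and an avid lesion need not reach 20 Gy at the capped activity. A reader might take the larger percentages in the table as the trial's false-positive rate; they are conditional on an assumed q that nothing in the article supports. Nor should weight be put on the Background's remark that refractory disease can mean absent uptake in only some lesions, because entry is governed by Table 2 and the tumour board.

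**Eligibility after treatment is a legitimate feasibility measure, and increased uptake also matters to the authors.** Both points stand. They are reasons to keep reporting overall eligibility and the dose change in baseline-eligible patients, but not to count those patients as restored.

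**Conclusion.** The mismatch is real. Section 2.6 sets no baseline condition, the aim and 2.4 concern restored or renewed uptake, and Table 2 leaves room for patients who meet the dose rule before lenvatinib. The paired tests in 2.9 limit the damage but do not resolve which count the 15% criterion judges. Five conversions without losses would meet that criterion and still give an exact McNemar p of 0.0625.

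The size depends on a share the documents do not give. If it is near zero, the effect is negligible. If one of five successes was already eligible, the lower limit falls from 15.2% to 9.9% (of 12) or 10.9% (of 11), and renewed uptake above 15% is no longer shown. These figures assume exact binomial intervals and independent patients; the table over q further assumes that baseline-eligible patients remain eligible.

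The fault lies in the definition of the primary endpoint and its criterion, not in the trial's ability to study restoration. The data needed are collected in every patient.

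**What to change.** 1. **2.6:** define primary success as not meeting the eligibility rule on baseline I-124 dosimetry and meeting it after lenvatinib. The rule that governs I-131 treatment itself is untouched.
2. **Denominator:** use patients ineligible at baseline. Keeping all 12 would count patients who cannot convert as failures: with q = 20% and 40% conversion the rate becomes 0.8 × 0.4 = 0.32, and the chance of 5 of 12 falls from 56% to 33%.
3. **2.4 and 2.9:** state that the 15% criterion applies to new conversions, and how it relates to the McNemar test, including the form of that test.
4. **Report separately:** the overall eligible fraction after lenvatinib, the number eligible at baseline, and the change in lesion dose in those patients.

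**Cost.** Wording in three sections; no extra scan or visit. If anyone is eligible at baseline, there are fewer evaluable patients and the interval widens. Five conversions are still needed with 12, 11 or 10 at risk (lower limits 15.2%, 16.8% and 18.7%). At a true conversion rate of 42%, the chance of reaching five is 61.7%, 52.2% and 41.8% respectively.
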